| 24-hour after surgery | Salivary amylase  HADS STAI  Visual analog scale for postoperative pain  QOR  Rescue analgesics usage |

※The allowable range is ± 12 hours before and 24 hours after surgery.

⑤ Sample size

In this study, we plan to perform Bayesian analysis. In this method, the posterior probability of the response rate is calculated by an interim analysis, and the calculated posterior probability is monitored. If it is judged that the effect is not as good as that of untreated, the test should be discontinued. Is planned. In addition, since the posterior predictive distribution is obtained based on the data obtained from the interim analysis, it is possible to judge whether the additional data follows the distribution, and it is possible to save the number of cases by performing this procedure. Is known to be. As an interim analysis, an exploratory analysis will be performed when 20 cases in a group are reached based on reference [1]. Recalculate the required number of cases based on the results of the interim analysis. Regarding the design of the number of cases, referring to the previous study, 1-β was 80%, the significance level was 0.05, and the success rate of the intervention group (yokukansan was expected to be taken preoperatively and preoperatively: impression at the outpatient clinic of pain clinic) is set to 75%. About 40 cases are expected in each group. The clinically meaningful difference is defined as σ = 0.3.

[1]Young-Chang Arai, et al, Evidence based Complementaly and Alternative Medicine.2014; ID965045

⑥ Study endpoints

Primary endpoint: Salivary amylase level

Secondary endpoint: HADS STAI QOR Pain VAS

⑦ Analysis method

Statistical analysis methods are planned to be performed by the maximum likelihood estimation method and the Bayesian statistical method. All analysis is performed by a person in charge of analysis different from that of the principal investigator.

For maximum likelihood estimation methods, t-tests that do not correspond to continuous variables, Fisher's exact test for scale classification, and Mann-Whitney U test for continuous variables or ordinal variables that do not follow a normal distribution such as VAS. A test will be used to determine P <0.05 as significant.

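### Agreement of later data with the interim predictive distribution says nothing about the treatment effect, so it cannot be a ground for saving cases

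*Protocol*

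**What the plan says.** Four statements in the protocol bear on this point. The first three are in section 4, ⑤ Sample size.

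- **The saving.** The interim data yield a posterior predictive distribution, from which "it is possible to judge whether the additional data follows the distribution, and it is possible to save the number of cases". The sentence goes on to attribute the saving to carrying out this procedure, and it is phrased as something known about the method.
- **The planned number and its basis.** "About 40 cases are expected in each group", with "1-β was 80%, the significance level was 0.05", a success rate of 75% in the yokukansan group, and "The clinically meaningful difference is defined as σ = 0.3".
- **The interim actions.** "an exploratory analysis will be performed when 20 cases in a group are reached". Then "If it is judged that the effect is not as good as that of untreated, the test should be discontinued", and "Recalculate the required number of cases based on the results of the interim analysis". No threshold, formula or minimum number accompanies any of these.
- **The final analysis.** ⑦ Analysis method uses the interim result as the prior and bases the final Bayesian analysis on 40 subjects in each group.

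**The concern.** A posterior predictive check asks whether new observations are compatible with a model fitted to the earlier ones. It does not ask whether the two groups differ. The two halves of a trial of an inactive treatment agree with each other just as well as the two halves of a trial of an effective one. As a ground for enrolling fewer patients, the check would therefore be met in nearly all trials and would carry no evidence about yokukansan.

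The planned power is at stake. The protocol leaves the sample size open to recalculation after the interim with no stated rule or floor. Apart from discontinuation for lack of effect, predictive agreement is the only route to a saving that it names.

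**Working it through.** **Inputs from the protocol (section 4, ⑤ and ⑦).** α = 0.05, power 80%, success rate 75% with yokukansan, meaningful difference 0.3, about 40 per group, interim at 20 in a group, uniform prior at the interim.

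**Assumptions.** α is two-sided. The 0.3 is a difference in success rates, so the control rate is 75% − 30% = 45%. The predictive interval is 95% (80% also tried). A further 10 or 20 patients per group are compared with the first 20. None of these is stated in the protocol.

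**Step 1. The plan's own number.** With rates 0.75 and 0.45, mean 0.60:

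n = [1.960·√(2·0.60·0.40) + 0.842·√(0.75·0.25 + 0.45·0.55)]² / 0.30² = (1.358 + 0.555)² / 0.09 ≈ 40.7, so 41 per group.

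This reproduces about 40. Reading 0.3 as a standardised mean difference gives 175 per group, so that reading does not fit.

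**Step 2. Pass rate of the check, continuous outcome.** Let d be the true difference in SD units. The interim difference is d + e₁ and the difference among the m later patients per group is d + e₂, where e₁ and e₂ are sampling errors. The check looks at (d + e₂) − (d + e₁) = e₂ − e₁. The effect d cancels. The remaining SD is √(2/20 + 2/m):

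- m = 10: √0.30 = 0.548 SD
- m = 20: √0.20 = 0.447 SD

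The pass rate is therefore fixed by the interval level. Simulation (50,000 trials per scenario, variance estimated from the interim data, predictive t-interval) gives 94.9% to 95.1% for d = 0, 0.3, 0.634 and 1.0, with m = 10 or 20.

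**Step 3. Pass rate of the check, success rates.** Uniform prior, exact beta-binomial predictive distribution, check on the difference between groups:

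| Interval, later patients per group | No effect (45% v 45%) | Planned effect (75% v 45%) | Reversed (45% v 75%) |
|---|---|---|---|
| 95%, 20 | 96.2% | 96.0% | 96.0% |
| 95%, 10 | 96.4% | 96.7% | 96.7% |
| 80%, 20 | 84.1% | 83.9% | 83.9% |

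The small differences come from the discreteness of counts.

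**Step 4. Power if the number were cut.** For a two-sided t-test, 40 per group has 80% power at d = 0.634. The non-centrality is 0.634·√(n/2), which is 2.84 at n = 40, 2.46 at n = 30 and 2.00 at n = 20. For the rates, power = Φ{[0.30·√n − 1.358] / 0.660}.

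| Per group | t-test, d = 0.634 | 75% v 45% |
|---|---|---|
| 40 | 80.0% | 79% |
| 30 | 67.5% | 67% |
| 20 | 49.8% | 49% |

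**Step 5. A quantity that does discriminate.** Take the predictive probability, at 20 per group, of a significant result at 40 per group. It is at least 0.9 in 0.9% of trials with no effect (45% v 45%) and in 34.2% with the planned effect. It is below 0.1 in 68.3% and 6.5% respectively. The cut-offs 0.9 and 0.1 are illustrative.

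**The case against.** The arithmetic is hardly open to dispute. The stronger objection is that the protocol does not contain the rule being criticised.

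- **No rule is stated.** A reader might infer that the trial will stop recruiting once later data agree with the interim distribution, and so would be cut short almost every time. The documents do not support that. The sentence reports what the method is known to allow and gives no interval level, number of added patients or instruction to stop. ⑦ Analysis method still plans 40 per group. This part of the objection stands.
- **A benign reading exists.** The check may be a compatibility check before the interim result is used as the prior for the final analysis, with cases saved because interim patients still count. Insensitivity to the effect would then be no defect. The text does not exclude this, but it does not say it either. As worded, it ties the saving to the check.
- **The translation is rough.** A predictive probability of success may have been meant, and that does discriminate (step 5). The text says something else, which is a reason to reword it.
- **The loss of power rests on assumed figures.** Neither 30 per group nor 0.63 SD is in the protocol. With 20 + 20 per group the check falls at the planned number and nothing is lost. This stands, so the figure of 67% is an illustration.
- **The recalculation is a separate instruction.** It is not tied to predictive agreement, and the criticism of the check does not cover it. It matters here only because it leaves the number open.

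**Conclusion.** The point holds in a limited form. Predictive agreement is given as a way to save cases, yet it carries no information on whether yokukansan works. A 95% check passes about 95% of the time at true effects from 0 to 1.0 SD, and 96% of the time for success rates with no effect, the planned effect or a reversed one. This result does not depend on the interval level or the number of later patients beyond the small variations shown.

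The consequence is conditional. If the number were reduced on this ground, for example to 30 per group, power would fall from about 80% to about 67%. That rests on the assumed stop at 30 and on the back-calculated 0.63 SD, or equally on 75% v an implied 45%. The protocol does not commit to such a reduction. It also does nothing to rule one out, since the recalculation has no stated rule or floor and no effect-based criterion takes the place of the check. The wording should be corrected.

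**What to change.** In section 4, ⑤ Sample size:

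1. Reword the sentence so that the posterior predictive check serves only as a model diagnostic, or as a check that the interim and later data are compatible.
2. State that the planned number, about 40 per group as in ⑦ Analysis method, is not reduced because of predictive agreement.
3. Make the recalculation sentence consistent with this. Any reduction should rest on a quantity tied to the treatment effect, such as the predictive probability of a successful final result. Its definition of success and its cut-off should be fixed before the interim data are seen.

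Items 1 and 2 are a change of wording. Item 3 needs a short decision on the criterion and, if the trial may end early for success, a check of the false-positive rate. The drawback is that the hoped-for saving in patients is not available through predictive agreement.

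### The number of cases is recalculated from a comparative interim, and the final tests stay at an ordinary P<0.05, so the stated 0.05 level is not protected

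*Protocol*

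**What the plan says.** Protocol section 4 item ④ describes an open-label superiority trial. Item ⑤ sets the design at "1-β was 80%, the significance level was 0.05", with a 75% success rate under yokukansan, and states "The clinically meaningful difference is defined as σ = 0.3" and "About 40 cases are expected in each group".

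For the interim, item ⑤ says "an exploratory analysis will be performed when 20 cases in a group are reached". The trial is to be discontinued if the treated effect is judged not as good as untreated, so the interim compares the groups. The text remarks of the Bayesian monitoring that "it is possible to save the number of cases by performing this procedure". It then gives the instruction "Recalculate the required number of cases based on the results of the interim analysis". It gives no formula, cap, minimum or restriction on which interim quantity may be used.

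Item ⑦ names the t-test, Fisher's exact test and the Mann-Whitney test, with one threshold: "A test will be used to determine P <0.05 as significant". Item ⑦ also plans a Bayesian estimate of the group difference for the primary endpoint, written for 40 subjects in each group.

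**The concern.** A fixed-sample test holds its nominal level when the sample size does not depend on the treatment difference seen so far. Here the size may be reset after that difference has been looked at. If a strong interim effect leads to a small second stage and a weak one to a large second stage, the weight of the first-stage data in the pooled test depends on how favourable they were. The pooled statistic is then no longer standard normal under the null.

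At stake is the error rate behind the superiority claim. The protocol designs to 0.05 and declares significance at 0.05, yet its own interim step allows rules under which the true rate is higher.

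**Working it through.** **Inputs from Protocol section 4 items ⑤ and ⑦.** Level 0.05 (sidedness not stated; two-sided assumed), power 80%, treated success rate 75%, difference 0.3, about 40 per group, interim at 20 per group, final threshold P<0.05. **Assumed, because the protocol gives none:** the recalculation rule, the caps (60 to 160 per group) and the minimum (40 or 22).

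**1. The plan's own figure.** Read 0.3 as a difference in success rates, so control = 0.75 − 0.30 = 0.45 and the mean rate is 0.60:

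n = [1.96·√(2·0.60·0.40) + 0.8416·√(0.75·0.25 + 0.45·0.55)]² / 0.30² = (1.358 + 0.555)² / 0.09 = 40.7, so 41 per group. Power at 40 per group is 79.3%. The stated 40 reproduces. Read as a standardised mean difference, 0.3 would need 175 per group, so the reading as proportions is the one that fits.

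**2. Recalculation on the observed effect.** With 20 per group, the standardised interim effect is d₁ = |z₁|·√(2/20). Sizing for 80% power at d₁:

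n = 2(1.96 + 0.84)² / d₁² = 20·2.80² / z₁² = 156.8 / z₁², then clipped to the minimum and cap.

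The pooled statistic is Z = √t·z₁ + √(1−t)·z₂ with t = 20/n. Before any clipping, z₁ = 1.0 gives n = 157 and a first-stage weight of √(20/157) = 0.36. At z₁ = 2.5, n = 25 and the weight is √(20/25) = 0.89. In a fixed design of 40 the weight is always √0.5 = 0.71.

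Given z₁, the chance that |Z| > 1.96 under the null is

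1 − Φ[(1.96 − √t·z₁)/√(1−t)] + Φ[(−1.96 − √t·z₁)/√(1−t)].

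Averaging this over z₁ ~ N(0,1) gives the two-sided error. Numerical integration and simulation agree to the precision shown:

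| Cap per group | Size can only grow from 40 | Size can also fall to 22 |
|---|---|---|
| 60 | 5.6% | 6.4% |
| 80 | 6.0% | 6.8% |
| 120 | 6.4% | 7.2% |
| 160 | 6.6% | 7.4% |

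With the size fixed at 40 the same calculation returns 5.0%. A binary-endpoint simulation (null rates 0.45 and 0.60, minimum 40 or 20, caps 40 to 160) gives 6.0-7.8%, against 5.3-5.6% for its own fixed design of 40. That baseline exceeds 5% because the data are discrete.

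**3. With the one stop the protocol states.** Suppose the stop is binding and is triggered by any interim effect below zero. Error on the benefit side, nominally 2.5%, is then 2.7-2.9% if the size can only grow and 3.1-3.3% if it can shrink to 22.

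**4. Recalculation on a nuisance parameter only.** If the within-group SD is re-estimated and the target difference is held, two-sided error is about 5.1% with minimum 40 and about 5.3% with minimum 22.

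**5. Fixed-weight combination.** With Z = √0.5·z₁ + √0.5·z₂ and weights set in advance, z₂ is standard normal under the null whatever the second-stage size. Z is therefore standard normal too. Simulated error is 5.0% at every cap.

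**The case against.** The strongest reply is that the protocol never says the observed effect drives the recalculation. It defines a clinically meaningful difference, and a team could hold that fixed and update only a variance or response rate. Step 4 shows that this does almost no harm. Some effect-based rules, such as increasing the size only after a promising interim, need not inflate the error either. This stands: a reader might infer that the 0.05 level is actually breached, but the text supports only that it is not protected.

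A reader might also infer that the trial may end early for success, which would inflate the error further. The documents do not support this. The only stop stated is for a treated effect not as good as untreated, and the interim is called exploratory. Likewise, the remark about saving cases describes what the Bayesian procedure is known to allow. It is not a rule that the size falls after a good result, so the may-shrink column shows a possibility the text leaves open.

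The stated stop does offset part of the inflation if it binds, but the protocol gives neither its threshold nor its binding status.

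Two replies carry less weight. The planned Bayesian analysis does not remove the issue, because the protocol also fixes frequentist tests, a 0.05 design level and a P<0.05 threshold. An SAP could add an adjustment, but the protocol itself sets an unrestricted recalculation beside an ordinary 0.05 test, and those two statements need reconciling where they stand.

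**Conclusion.** The point holds in this form: the protocol allows the size to be reset from a comparative interim in an open-label trial, does not confine this to a nuisance parameter, and tests at an ordinary 0.05. The level is not protected.

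The possible inflation is moderate: about 5.6-7.4% two-sided if the observed effect sets the size. It is smaller on the benefit side with a binding stop (2.7-3.3% against 2.5%) and negligible if only the SD is updated. All of these figures rest on assumed rules, caps and minimums, on a two-sided 0.05 and on reading the interim as 20 per group. That the recalculation uses unblinded results is inferred from the open-label design and the treated-versus-untreated comparison, and that the final test pools both stages is inferred from the ordinary tests named. The point merits a change before the interim and does not by itself undermine the trial.

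**What to change.** Choose one and write it into Protocol section 4 items ⑤ and ⑦ before the interim.

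- **(a) Nuisance parameter only.** Recalculate from a blinded pooled quantity, computed without using group labels: the pooled SD of the primary endpoint, or the pooled response rate if the size remains based on success rates. Keep the prespecified target difference and make 40 per group the minimum. The ordinary final test can then stay. Cost: any reduction below 40 per group is given up.
- **(b) Observed effect allowed.** Make the final primary test an inverse-normal combination of stage 1 (first 20 per group) and stage 2 (all later patients), with weights fixed in advance at √0.5 each. This holds 5.0% whatever the recalculated size. Cost: a little efficiency if the size moves far from 40. At 40 per group the weights match those of the pooled test.

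In either case, state that no success claim is made at the interim. Both options are changes of wording.

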**4. [Research method and period]**

① Research implementation period

From November 1, 2017 to March 31, 2021.

② Information on drugs used

Name: Tsumura Yokukansan (Product number: 054)

Route of administration, dosage and administration: Oral, 1 packet (2.5 g) at a time

Dosage form: Extract granules

③ Research subjects

Patients aged 20 to 60 years who undergo breast cancer surgery at Niigata University Medical and Dental Hospital or Niigata Prefectural Cancer Center Niigata Hospital and undergo total mastectomy and sentinel lymph node biopsy, or partial mastectomy and sentinel lymph node biopsy (Details will be described later).

④ Research method

Multicenter / Open Label / Superiority test by forced random sampling

[1] A pre-treatment questionnaire survey will be conducted on all subjects, and the age, BMI, surgical history, and general status (American Society of Anesthesiologists-Physical Status: ASA-PS, ECOG-PS) will be recorded in advance. Also, before taking the study drug, record the measurement of amylase in saliva, the Hospital anxiety and depression scale (HADS), and the State Trait Anxiety Inventory (STAI).

[2] Subjects are assigned to two groups, one with yokukansan (intervention) and the other without (control), according to the results of randomization. The intervention group should be given 1 packet (2.5 g) of TSUMURA Yokukansan before sleep on the day before surgery and 1 packet (2.5 g) 2 hours before entering the operating room on the day of surgery. For the purpose of maintaining the same quality between the two groups, a forced allocation algorithm is created, and if a bias is confirmed between the groups, forced allocation is performed based on age, surgical history, etc.

[3] Subjects in the intervention group take 1 packet of yokukansan orally 2 hours before entering the operating room on the day of surgery, and then all participants are measured salivary amylase in the operating room. Anesthetized by general anesthesia in the operating room and undergo total or partial mastectomy and sentinel lymph node biopsy

[4] Record salivary amylase measurements, HADS, STAI, visual analog scale of pain: VAS, QOR (Quality of recovery), and the presence or absence of analgesic use 24 hours after surgery.

| 24-hour before surgery | Salivary amylase  HADS STAI |
| --- | --- |
| Just before surgery | Salivary amylase |

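### The 80% power for about 40 per group is calculated for an undefined success rate, so it is not established for the primary endpoint, salivary amylase level

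*Protocol*

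**What the plan says.** Protocol section 4 ⑤ (Sample size) gives these inputs: "referring to the previous study, 1-β was 80%, the significance level was 0.05, and the success rate of the intervention group", which is set at 75%. The source of the 75% is described as "impression at the outpatient clinic of pain clinic". The result and the effect size follow: "About 40 cases are expected in each group. The clinically meaningful difference is defined as σ = 0.3". Neither success nor a control-group rate is defined. The same section plans an interim analysis at 20 cases in a group. That analysis monitors the posterior probability of a response rate, also undefined, and the required number of cases is then recalculated.

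Section 4 ⑥ (Study endpoints) states "Primary endpoint: Salivary amylase level". Section 4 ⑦ (Analysis method) lists a t-test or Mann-Whitney test for continuous variables, with the rule "A test will be used to determine P <0.05 as significant". It adds a Bayesian estimate of the difference between the two groups on the primary endpoint. The procedures for missing data exclude any patient whose primary endpoint is missing.

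**The concern.** A sample size calculation should concern the variable and the comparison on which the trial's conclusion rests. Here the inputs are a proportion and a difference that makes sense as a gap between proportions, while the primary endpoint is a measured level. Nothing in the protocol turns that level into success or failure, so the two cannot be connected.

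The 80% will be used to interpret the result. If the amylase comparison is not significant, a reader will take it that the trial had an 80% chance of finding a clinically meaningful effect. That chance was never calculated for amylase, and the meaningful difference is not expressed in amylase units. The interim monitoring and the recalculation inherit the problem, because they too refer to an undefined response.

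This is more than a detail that can be left to a statistical analysis plan. The protocol does present a calculation, and the calculation is for a different kind of variable from its own primary endpoint.

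**Working it through.** **Inputs.** From section 4 ⑤: power 80%, significance level 0.05, intervention success rate 0.75, meaningful difference 0.3, about 40 per group in equal groups. Not stated, hence assumed: two-sided testing, and a control rate of 0.75 − 0.30 = 0.45. The normal quantiles are 1.960 (two-sided 0.05) and 0.842 (80% power).

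**Step 1: reproduce the plan's figure as two proportions.**

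- Pooled formula: n = [1.960·√(2·p̄(1−p̄)) + 0.842·√(p₁(1−p₁) + p₂(1−p₂))]² / (p₁−p₂)², with p̄ = 0.60. The numerator is [1.960·√0.48 + 0.842·√(0.1875 + 0.2475)]² = (1.358 + 0.555)² = 3.660. Divided by 0.09 this is 40.7, so 41 per group.
- Unpooled formula: n = (1.960 + 0.842)²·0.435 / 0.09 = 37.9, so 38 per group.
- Power of the pooled z-test at 40 per group: 79.3%.

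This fits about 40. It depends on the inferred control rate: by the pooled formula, a control rate of 40% gives 31 per group and 50% gives 58.

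**Step 2: compare with the primary endpoint.** The calculation needs a success criterion and a control rate. Section 4 ⑥ names a level, and section 4 ⑦ compares groups on it. The protocol contains no amylase cut-off, no amylase SD and no expected amylase difference. The 80% therefore cannot be carried over to amylase, and the power for amylase cannot be computed from the protocol.

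**Step 3: what 40 per group can detect on a continuous endpoint.** With d the true difference in SD units, the detectable d at 80% power is (1.960 + 0.842)·√(2/40) = 0.626 by the normal approximation, and 0.634 for the t-test. Power of the two-sided 0.05 t-test with 40 analysed per group:

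| True difference | Power |
|---|---|
| 0.5 SD | 60% |
| 0.634 SD | 80% |
| 0.7 SD | 87% |

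**Step 4: effect of loss.** Section 4 ⑤ states no allowance for loss. Patients without the primary endpoint are excluded, and section 5 (3) cancels participation when a positive sentinel node leads to axillary dissection. The loss rate is not given. Assuming 10% to 20%, 40·0.9 = 36 or 40·0.8 = 32 per group are analysed, and power at 0.634 SD falls to 76% or 70%.

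**The case against.** **The number is arithmetically sound on its own terms.** This stands. With the inferred 45%, 40 per group gives 79.3% power by the pooled z-test. The fault lies in the variable, not in the arithmetic.

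**Forty is provisional, because the size is to be recalculated after the interim analysis.** True, but the recalculation is not tied to amylase and the quantity monitored is again an undefined response rate. As written, it carries the mismatch forward.

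**The primary analysis is partly Bayesian, so frequentist power matters less.** The protocol nevertheless claims 80% power at 0.05 and applies a significance rule, so the figure should be right for what it describes.

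**A cut-off may stand in a document not seen here.** Possibly, but the protocol names the level itself as primary endpoint and plans a group difference on it.

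Some stronger readings are tempting and not supported:

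- A reader might infer that the trial lacks the power it claims. Without an SD or expected difference this is not shown; power is 80% or more if the true difference is about 0.63 SD or larger.
- A reader might take the value 0.3, labelled σ, as 0.3 SD, which would need 176 per group and give 26% power at 40. But 0.3 stands beside a 75% rate and reproduces about 40 as a gap between proportions, so that reading is not the source of the number.
- A reader might object that Fisher's exact test has only 73% power at 40 per group for 75% against 45%. Section 4 ⑦ assigns that test to categorical scales, not to the primary endpoint.
- A reader might infer that moderate effects would probably be missed. At 0.5 SD the power is 60%, so detection is more likely than not.

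**Conclusion.** The concern holds in this form: the 80% power with about 40 per group is derived for an undefined binary success rate, and is not established for the continuous primary endpoint. The planned recalculation does not repair this.

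The size can be given only in SD units: 80% power at about 0.63 SD with 40 analysed per group, and less for smaller differences or after losses. Whether 0.63 SD of salivary amylase is a clinically meaningful or realistic difference cannot be judged from the protocol.

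The conclusion on the mismatch rests on the protocol's text alone. The reproduction of 40 rests on the inferred 45% control rate and two-sided testing. The SD-scale figures rest on a two-sided t-test with roughly normal data and equal groups, and the loss figures on an assumed 10% to 20%.

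**What to change.** Keep about 40 per group and replace the success-rate justification in section 4 ⑤ with one for amylase, for example: *With 40 patients analysed per group, a two-sided 0.05 t-test has 80% power for a difference of about 0.63 SD in salivary amylase, and 60% for 0.5 SD. With 36 or 32 analysed per group (assumed loss of 10% or 20%), power at about 0.63 SD is 76% or 70%.*

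In addition:

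- State the clinically meaningful difference in amylase units with the assumed SD, in place of the value 0.3.
- Define the interim monitoring and the sample size recalculation on amylase.

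Alternatively, if a responder analysis is intended, define success on amylase, state the control rate, and make that comparison the primary one.

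The first route changes wording only and needs no extra patients, provided 40 is understood as the number enrolled and the loss figures are reported alongside. If 40 analysed per group is to be guaranteed, the same assumed loss means enrolling 40/0.9 ≈ 45 to 40/0.8 = 50 per group. The price of either reading is a stated power less favourable than the present 80%.

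### The primary endpoint, salivary amylase, names no time point or summary measure although two post-dose samples are taken, and the protocol does not say clearly whether the frequentist or the Bayesian analysis decides

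*Protocol*

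**What the plan says.** The definition in Protocol section 4 ⑥ is complete in four words: "Primary endpoint: Salivary amylase level". It gives no time point, no change from baseline and no summary over time.

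Section 4 ④ and its schedule table provide three measurements of that variable:

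- Pre-dose: "before taking the study drug, record the measurement of amylase in saliva".
- Just before surgery, after the second dose in the intervention group: "all participants are measured salivary amylase in the operating room".
- 24 hours after surgery, together with the questionnaires and pain score: "Record salivary amylase measurements, HADS, STAI, visual analog scale of pain: VAS, QOR". A note under the table sets the timing window: "The allowable range is ± 12 hours before and 24 hours after surgery".

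Section 4 ⑦ says that the analyses are "planned to be performed by the maximum likelihood estimation method and the Bayesian statistical method". For the frequentist part it lists unpaired tests by type of variable and one criterion: "A test will be used to determine P <0.05 as significant". For the Bayesian part it says that the group difference in the primary endpoint is estimated, and it gives no posterior threshold for success. None of the listed tests uses the pre-dose amylase value.

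The paragraph on missing, rejected and abnormal data, which follows section 12, removes from the analysis any patient whose primary endpoint is missing.

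**The concern.** The two post-dose samples answer different questions. The operating-room value reflects stress shortly after dosing, before anaesthesia and surgery. The 24-hour value follows surgery, anaesthesia and any rescue analgesia. A result at one cannot stand in for a result at the other.

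Three things are at stake:

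- **Choice after the fact.** With no time point fixed and only an unadjusted P<0.05 criterion, whichever post-dose value looks better could be presented as the primary result.
- **The analysis set.** A patient with an operating-room value but no 24-hour value is either analysed or excluded, depending on a choice that the protocol does not make.
- **Conflicting results.** The primary endpoint is to be analysed in two frameworks. If they disagree, the protocol gives no clear reading.

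**Working it through.** **1. Can the time point be inferred from elsewhere in the protocol?**

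- Amylase is the only measure taken just before surgery, which points to the operating-room sample.
- The title and aim concern perioperative anxiety and pain, and every secondary endpoint is recorded at 24 hours after surgery, which points to the later sample.
- The sample size in section 4 ⑤ does not help. It uses a success rate of 75% that is not defined on amylase or at any time. If the stated meaningful difference of 0.3 is read as an absolute difference (an assumption), the control rate is 0.75 − 0.30 = 0.45 and the pooled rate is 0.60. With two-sided alpha 0.05 and 80% power:

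  n = [1.96·√(2·0.60·0.40) + 0.8416·√(0.75·0.25 + 0.45·0.55)]² / 0.30² = 40.7, so 41 per group.

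  This agrees with the stated figure of about 40. Power at exactly 40 per group is 79.3%. The trial is therefore sized for a single comparison at 0.05, but which comparison is not stated.

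The document does not settle the time point.

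**2. What would it cost if success at either post-dose sample counted?**

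Inputs: two post-dose samples (section 4 ④) and P<0.05 for each test (section 4 ⑦). Two-sided testing is assumed because the sidedness is not stated. The correlation ρ between the two test statistics is not in the documents, so a range is shown.

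- Two-sided: P(at least one rejection) = 0.05 + 0.05 − P(both reject). At ρ = 0 this is 1 − 0.95² = 0.0975.
- In favour of the drug only: 0.025 + 0.025 − P(both reject in favour). At ρ = 0 this is 1 − 0.975² = 0.0494.

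For other ρ the joint probability comes from the bivariate normal distribution:

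| ρ (assumed) | Both reject, two-sided | Either rejects, two-sided | Either rejects, in favour of drug |
|---|---|---|---|
| 0 | 0.0025 | 0.0975 | 0.0494 |
| 0.3 | 0.0049 | 0.0951 | 0.0476 |
| 0.5 | 0.0093 | 0.0907 | 0.0454 |
| 0.7 | 0.0165 | 0.0835 | 0.0417 |
| 0.9 | 0.0296 | 0.0704 | 0.0352 |

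The reference values for one named time point are 0.05 and 0.025.

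**3. What if both samples were kept as alternative routes to success?**

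With Bonferroni at 0.025 each, the same formula (2.2414 in place of 1.96) gives 49.4, so 50 per group. Power at 40 per group falls to 69.9%. With one named time point the requirement stays at 41.

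**4. Which framework decides?**

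Section 4 ⑤ opens by saying that the trial will be analysed by Bayesian methods and bases its interim monitoring on the posterior. Section 4 ⑦ ties the Bayesian estimate to the primary endpoint. On the other side, section 4 ⑤ sizes the trial by significance level 0.05 and 80% power, and section 4 ⑦ keeps P<0.05. The text points both ways. The Bayesian route has no P value and no stated threshold, so no error rate can be attached to it from the document.

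**The case against.** The strongest reply is that the protocol names one primary endpoint, one alpha and one sample size, and speaks of the group difference in the singular. A single time point, a change score or a repeated-measures contrast would all fit that wording. Details such as multiplicity adjustment and a posterior threshold are commonly left to the SAP, which is not shown.

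Much of this stands, and it rules out several stronger readings that a reader might infer:

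- *Both post-dose values are primary and each will be tested at 0.05.* No section says so. The text permits that use but does not plan it.
- *The two frameworks have equal standing.* This is not stated. A reading in which the Bayesian analysis is primary is available from section 4 ⑤; the alpha, power and P<0.05 statements keep it unsettled.
- *The Bayesian analysis is a further chance to succeed at P<0.05.* It has no P value. With a flat prior and a posterior probability rule of 0.975, it would add essentially nothing to the error rate.
- *The prior built from 20 subjects counts the same data twice and so inflates the error.* That depends on one reading of section 4 ⑦ and on an assumed success rule. It is also a separate matter from the missing time point.
- *The chance of a false claim of benefit exceeds 5%.* Counting only results in favour of the drug, it stays just below 5% even at correlation 0.

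What does not stand is leaving the time point to the SAP. It defines the trial's question, and the protocol's own missing-data exclusion cannot be applied without it.

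**Conclusion.** The concern holds as an undefined primary endpoint. Four words cover three scheduled samples, two of them after dosing, and the rest of the protocol does not show which is meant. Two consequences follow directly from the text: either post-dose value could be reported as primary at P<0.05, and the exclusion for missing primary data has no fixed meaning.

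The error inflation is conditional. It applies only if success at either sample counts, and its size rests on two-sided tests and assumed correlations: about 7% to 10% instead of 5%, or about 3.5% to 4.9% instead of 2.5% in favour of the drug. The unclear choice of framework is a further ambiguity, with no figure attached. The sponsor should correct this; it does not require a change to the data collected.

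**What to change.** Before any results are seen:

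1. In section 4 ⑥, name one primary time point. The operating-room sample is a reasonable choice, because it is the one closest to dosing and precedes anaesthesia and surgery. The documents do not make it the only possible choice; what matters is that one is fixed. List the other post-dose amylase value as secondary.
2. In section 4 ⑦, analyse the named value adjusted for the pre-dose amylase, which is already collected, in place of an unpaired comparison that ignores it.
3. In the missing-data paragraph after section 12, state that the exclusion refers to the named sample.
4. State which framework decides for the primary endpoint and label the other supportive. This must agree with section 4 ⑤, where interim monitoring uses the posterior. If the frequentist test is made decisive, the wording there needs to be aligned too.

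Cost: a few sentences in sections 4 ⑤ to ⑦ and in the missing-data paragraph, with no new measurements and no additional patients for this point. The downside is that the other amylase value loses primary status. Keeping both as alternative routes to success would instead need about 50 per group under the assumptions above.
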